### Eligibility criteria

People aged between 40 and 60 years, with three criteria for MS [1], with IR according to the homeostatic model assessment (HOMA-IR) greater than 2.25 [29, 30] and with a sedentary lifestyle [31] will be included. People with a vegetarian diet, supplemental consumption of vitamin D3, injuries or musculoskeletal diseases that prevent exercise; people in a situation of physical, sensory and cognitive disability; people with a history of cardiopulmonary disease or acute or chronic inflammatory conditions, cancer, acquired immune deficiency syndrome or diabetes mellitus; and pregnant women will be excluded.

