#### Insulin resistance

HOMA-IR will be used to estimate IR, insulin sensitivity (IS) and the percentage of functioning pancreatic β cells (% β) [35]. HOMA-IR will be calculated before and between 44 and 48 h after the last session of the exercise training program, from the blood glucose and insulinemia values obtained from a venous blood sample taken after fasting for 8–12 h [35]. The measurement of insulinemia will be performed with the sandwich immunoassay technique with direct chemiluminescence technology with an ADVIA Centaur® CP Immunoassay System (Siemens, Germany).

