### Sample size

A total required sample size of 30 people in each group was calculated assuming an IS increase of 10% [39], 15% standard deviation [5], a 95% confidence level, 80% power, a 1:1 ratio, and a dropout rate of 5%. In addition, a correlation coefficient of 0.44 between the baseline and final IS values was taken into account [40].

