### Statistical analysis

Initially, an exploratory analysis of the data will be carried out, and the Shapiro-Wilk test will be used to evaluate if the quantitative variables come from a population with a normal distribution. The mean and the standard deviation, the median and the interquartile range and the percentage will be used for the description of the socio-demographic, clinical, anthropometric and physiological variables of the included persons.

Both intention-to-treat and by-protocol analyses will be carried out; the latter will consider those patients who had adherence higher than 80%. The multiple imputation method (10 imputations) will be used to manage missing data based on age, gender, BMI and baseline VO_2_ max [44].

Analysis of covariance (ANCOVA) will be used [45] to estimate the effect of HIIT-low volume compared to CAE on IR, IS, percentage of pancreatic β-cell functioning, plasma levels of musclin and apelin and mass and composition of thigh muscle by fiber type at the end of the intervention. The assumptions of homogeneity of variance will be assessed with the Levene F test and the linearity and homogeneity of the slopes. If the assumptions are not met, a logarithmic transformation will be performed, or the Box-Cox procedure will be used. The variables used in the minimization procedure (age, gender and BMI) will be included in the analysis according to the current recommendations [41]. A re-randomization test will be performed using permutations for inference purposes [41].

To establish if the musclin, apelin, muscle mass and fiber type composition of the thigh mediate the effect of training on IR, a theoretical model was proposed to estimate the total, direct and indirect effects and the percentage explained by the mediator (Fig. 3). A model of structural equations will be used with the “path analysis” technique and basic principles proposed in the context of clinical trials [46–48]. A statistical significance level œ = 0.05 will be established, and STATA, version 14.0, and IBM SPSS Statistics, version 21.0, will be used.

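### Assumption checks on the trial data decide whether HOMA outcomes are analysed raw, log-transformed or Box-Cox-transformed, so the effect measure is not fixed in advance

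*Protocol article*

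**What the plan says.** All of this comes from the protocol article.

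- **Statistical analysis, model.** ANCOVA at the end of the intervention is used "to estimate the effect of HIIT-low volume compared to CAE on IR, IS, percentage of pancreatic β-cell functioning", the two myokines, and thigh muscle mass and composition. No scale is named, so untransformed values are the implied default.
- **Statistical analysis, checks.** "The assumptions of homogeneity of variance will be assessed with the Levene F test and the linearity and homogeneity of the slopes". The next sentence is the rule at issue: "If the assumptions are not met, a logarithmic transformation will be performed, or the Box-Cox procedure will be used". There is no criterion for choosing log over Box-Cox, no fixed exponent, and no further step if a check still fails after transformation.
- **Statistical analysis, other steps.** A Shapiro-Wilk test of the quantitative variables is part of the exploratory work. The section also plans intention-to-treat and per-protocol analyses, 10 imputations, a path model for mediation, and this safeguard: "A re-randomization test will be performed using permutations for inference purposes".
- **Insulin resistance.** HOMA, calculated from fasting glucose and insulin, supplies IR, IS and the beta-cell percentage.
- **Eligibility criteria.** Participants enter "with IR according to the homeostatic model assessment (HOMA-IR) greater than 2.25".
- **Sample size.** The planning effect is a 10% increase in IS with a 15% SD and a baseline-to-final correlation of 0.44.

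**The concern.** The scale of a treatment effect is part of its definition. Under this rule the scale is known only after outcome data have passed or failed tests, with about 30 participants per arm. One trial could report a difference in HOMA units. Another, run to the same plan, could report a ratio of geometric means, or a difference in powers of HOMA with an estimated exponent and no clinical unit.

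The rule also sits badly with the rest of the section:

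- The intention-to-treat and per-protocol sets can fall into different branches and then cannot be compared.
- The checks or the Box-Cox exponent can differ between the 10 imputed datasets, and estimates on different scales cannot be pooled.
- The total effect in the path model need not be on the ANCOVA scale.

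Finally, transformation is the only remedy named for three different failures, and unequal slopes or variances are not always a matter of scale.

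**Working it through.** **1. The plan's own figure.** Inputs from Sample size: difference 10, SD 15, r = 0.44, 80% power, 95% confidence (taken as two-sided), 5% dropout.

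- n per arm = 2 × (1.960 + 0.842)² × (15/10)² = 35.32
- ANCOVA factor: 35.32 × (1 − 0.44²) = 35.32 × 0.8064 = 28.48
- Dropout: 28.48 / 0.95 = 29.98, so 30 per arm

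The stated 30 reproduces and this point does not change it. The article does not say whether 10% and 15% are percentage points or relative change, so the calculation does not settle the scale.

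**2. How often the rule would switch scale, and whether switching repairs the failure.** Simulation with 30 per arm and 3,000 trials per scenario. Assumptions not in the article: log-normal HOMA-IR, baseline above 2.25, log-SD 0.4 (before the entry cut), residual log-SD 0.4, log slope 0.6 (1.0 in one arm and 0.2 in the other for the interaction row). Each check is at 0.05.

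| Scenario | Any raw check fails | Levene fails, raw → log | Slopes fail, raw → log |
|---|---|---|---|
| No effect | 28% | 9% → 5% | 11% → 5% |
| 25% reduction, multiplicative | 44% | 25% → 5% | 13% → 5% |
| 50% reduction, multiplicative | 87% | 79% → 5% | 25% → 5% |
| True baseline-by-treatment interaction | 81% | 12% → 4% | 75% → 66% |
| Log-scale SD 0.25 v 0.60 between arms | 97% | 96% → 98% | 11% → 6% |

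For a multiplicative effect, log brings failures back to the 5% expected by chance. For a true interaction, 84% of raw slope failures persist on log. For truly unequal log-scale variances, 99% of raw Levene failures persist.

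**3. The branches answer different questions.** In the last row the arms have equal medians given baseline, but their arithmetic means differ by a factor exp[(0.60² − 0.25²)/2] = exp(0.149) = 1.16. The raw analysis rejects in 13.6% of trials and the log analysis in 4.8%. Both can be right, because they test different contrasts.

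**4. Type I error.** Under no effect, going to log when a raw check fails gives 0.046. Taking the smaller p-value of log and Box-Cox after a failure also gives 0.046.

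**5. Power.** 57 participants (60 × 0.95), log-normal HOMA-IR truncated at 2.25, assumed median 3.2, r = 0.44.

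| Log-SD, effect | Fixed log | Protocol's rule | Always raw IR |
|---|---|---|---|
| 0.5, 25% reduction | 65% | 60% | 59% |
| 0.4, 25% reduction | 83% | 80% | 80% |
| 0.15, 10% effect | 74% | – | 73% |

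The rule loses 65 − 60 = 5 and 83 − 80 = 3 points. Staying raw throughout loses up to 65 − 59 = 6. At the protocol's planning values the gap is 74 − 73 = 1. In the 25% scenarios the rule left the raw scale in about 45% of trials. That share depends on how each check is done, which the article does not define.

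**The case against.** Checking assumptions and then transforming is conventional, and a condensed article may leave the choice of transformation, the exponent and back-transformation to a fuller plan. That covers missing detail. It does not cover a selection rule that the article itself states, with two alternatives and no criterion.

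Four further objections have force:

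- **A reader might infer that transformation does not repair the failures tested for.** That is too strong. For a multiplicative effect, log repairs them almost entirely. Only a true interaction or a true variance difference tends to survive.
- **A reader might infer an inflated type I error.** Picking whichever of raw IR, raw IS and log is significant gives 5.9% to 7.9%. The article's trigger is a failed assumption, not significance, and IS is a separately listed outcome. The rule as written stays near 5%.
- **Log is not proved to be the correct scale.** The article gives no HOMA formula, the 10% and 15% can be read two ways, and an entry cut-off is no argument for log. What supports log is that HOMA-IR is calculated from two positive measurements and that the planning figures are percentages. That makes log a reasonable choice to fix in advance.
- **The re-randomization test protects type I error.** It can, if the scale selection is repeated within each re-randomization, which is not stated. It cannot define the effect measure.

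**Conclusion.** The point holds in a limited form and is minor. The rule makes the scale of the HOMA effect depend on the data, leaves the choice between log and Box-Cox open, and names no remedy for interaction or unequal variance that survives transformation. The documents do not support a claim of inflated false-positive risk or of an invalid sample size.

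The main cost is an effect measure that is undefined until the data are seen and that may differ between analysis sets. The second cost is power: about 3 to 6 points against a fixed log analysis if HOMA-IR is log-normal with log-SD 0.4 to 0.5 and the effect is a 25% reduction, and about 1 point at the protocol's planning values. The distribution, median, log-SD and 25% effect are assumptions; the article gives none of them.

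**What to change.** Replace the conditional rule with fixed choices:

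- **HOMA-IR, musclin and apelin:** ANCOVA on the natural-log scale with log baseline as covariate plus the minimization factors, reported as geometric-mean ratios with 95% CI. If IS is defined as the reciprocal of HOMA-IR (no formula is given), the same analysis gives its ratio and the same p-value.
- **Every remaining outcome** (beta-cell percentage, thigh muscle mass, fibre composition, and IS if defined otherwise): name one scale now.
- **Box-Cox:** delete the branch.
- **Levene, linearity and slope checks:** keep as diagnostics that do not change the main analysis. Use heteroscedasticity-robust standard errors alongside the planned re-randomization test, and report any baseline-by-treatment interaction as a sensitivity analysis.
- **Consistency:** use the same scale in the intention-to-treat, per-protocol, imputed and path-model analyses.

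This is a change of wording, with no effect on sample size or data collection, provided that it is made before outcomes are examined by arm. The downside is that these effects are reported as ratios rather than in HOMA units. Back-transformed geometric means by arm would help clinical readers.

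### The 30-per-arm sample size relies on adjustment for the baseline outcome, but the ANCOVA description names only age, gender and BMI as covariates

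*Protocol article*

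**What the plan says.** The Sample size section of the protocol article gives 30 people per group. Its inputs are a 10% increase in insulin sensitivity (IS), a 15% standard deviation, 95% confidence, 80% power, 1:1 allocation and 5% dropout. It adds that "a correlation coefficient of 0.44 between the baseline and final IS values was taken into account".

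The Statistical analysis section chooses ANCOVA to compare the arms on insulin resistance, IS, beta-cell function, musclin, apelin, and thigh muscle mass and composition after the 12 weeks. It plans checks of equal variances, linearity and parallel slopes. On covariates it says: "The variables used in the minimization procedure (age, gender and BMI) will be included in the analysis". A permutation-based re-randomisation test follows, with no test statistic or model specified. On the error rate: "A statistical significance level œ = 0.05 will be established".

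No section names the baseline value of IS, or of any other outcome, as a covariate.

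**The concern.** A correlation between baseline and final values reduces the required sample size only if the analysis uses the baseline value. The Sample size section takes credit for that correlation, whereas the Statistical analysis section lists covariates without the one that earns the credit. An analyst who fits exactly the covariates named would run a less precise comparison than the one the trial was sized for. The choice would also still be open when the data are in hand. At stake are some points of power in a 60-patient trial, and a model for the main comparison that two competent readers could fit differently.

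**Working it through.** **Inputs, all from the Sample size section.** Difference δ = 10, SD σ = 15, power 80%, dropout 5%, baseline–final correlation r = 0.44. The 95% confidence level is taken as two-sided α = 0.05; sidedness is not stated. The 10% is read as the between-arm difference, on the same scale as the SD.

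**Step 1: reproduce the stated 30.** With no use of baseline,

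n = 2(1.96 + 0.8416)² × (15/10)² = 35.32 per arm.

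ANCOVA on the baseline value multiplies the outcome variance by 1 − r² = 1 − 0.1936 = 0.8064:

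35.32 × 0.8064 = 28.48, and 28.48 / 0.95 = 29.98, which rounds to 30.

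This is the stated figure. (Rounding up to 29 before inflating for dropout gives 31, a difference of rounding only.)

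**Step 2: try the alternatives.**

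| Reading | n per arm | After 5% dropout |
|---|---|---|
| Two-sided, baseline-adjusted | 28.48 | 29.98 |
| Two-sided, final values, r unused | 35.32 | 37.2 |
| Two-sided, change score, variance factor 2(1 − r) = 1.12 | 39.56 | 41.6 |
| One-sided 0.05, final values, r unused | 27.8 | 29.3 |

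The one-sided row can be rounded up to 30, but it leaves r = 0.44 unused, and the article says that r was used. Among the two-sided readings only baseline adjustment gives 30.

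**Step 3: power with and without the baseline covariate.** Analysed per arm: 30 × 0.95 = 28.5. By normal approximation, power = Φ(δ / (s√(2/m)) − 1.96), with m the number analysed per arm and s the residual SD.

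- Baseline in the model: s = 15√0.8064 = 13.47; 10 / (13.47 × √(2/28.5)) = 2.80; power 80.0% (noncentral t 78.6%).
- Baseline absent, named covariates explaining nothing: s = 15; 10 / (15 × √(2/28.5)) = 2.52; power 71.1% (noncentral t 69.6%, or 69.5% after three degrees of freedom for the covariates).

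On the same method, the loss is about 9 points: 80.0 to 71.1, or 78.6 to 69.6. With 28 to 30 analysed per arm, power without baseline is 70 to 73% (normal) or 69 to 72% (t).

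**Step 4: allow for age, gender and BMI.** The article does not say how much variance these three explain, so the shares below are assumptions, with s = 15√(1 − R²) and 28.5 per arm.

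| Assumed R² of age, gender, BMI | Power, normal | Power, noncentral t |
|---|---|---|
| 0% | 71.1% | 69.5% |
| 5% | 73.3% | 71.7% |
| 10% | 75.6% | 74.0% |
| 15% | 77.9% | 76.4% |
| 19.36% (= r²) | 80.0% | 78.5% |

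The three factors would have to explain about 19% of the variance, the share credited to baseline, to restore the planned power by themselves.

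**The case against.** The strongest reply is that baseline adjustment is already implied. The sentence on the minimisation factors answers a narrower question, namely how to respect the allocation method, and does not say the list is complete. ANCOVA and the slopes checks are introduced before that sentence. The section on random assignment defines all three minimisation factors as two-level categories, so a check of linearity suggests that some continuous covariate is already in the model. The sample size itself shows that its authors had baseline adjustment in mind. In addition, an article condenses a fuller protocol, and a complete covariate list is commonly left to the SAP.

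Much of this stands. A reader might infer that the plan omits the baseline value and that the trial therefore has 70% power. The text supports neither: it is silent rather than exclusive, and 70% is the bottom of a range that assumes three prognostic-looking covariates explain nothing. A reader might also set the design against a change-score analysis, but the article plans none. Nor can one say that the re-randomisation test carries over the same gap, because no model is stated for it.

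Two things are left. The slopes checks do not settle the matter, since age and BMI could be entered as continuous. And the article does name covariates, so the point is a mismatch between two stated sections rather than a complaint about detail left to another document.

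**Conclusion.** The point holds as a covariate that the sample size depends on and that the analysis description does not name. It does not show that the fitted model will leave baseline out. If only the named covariates are used, power for IS at 28.5 analysed per arm is about 71% (70% by noncentral t) when they explain no variance and about 73 to 78% (72 to 76%) when they explain 5 to 15%, against 80% (78.6%) with baseline adjustment. The like-for-like loss is therefore at most about 9 points.

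These figures rest on a two-sided 5% test, on the article's own 10, 15 and 0.44, and on 5% dropout reducing the number analysed. They apply to IS only, since no baseline–final correlation is given for the other outcomes. This is an improvement available at no cost, not a flaw that undermines the trial.

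**What to change.** In the Statistical analysis section, state: *For each outcome, the ANCOVA on the 12-week value includes treatment, the baseline value of that outcome on the same scale (transformed in the same way if a transformation is used), age, gender and BMI. The re-randomisation test uses the treatment statistic from this model.*

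The sample size stays at 30 per arm, because it already assumes this model. IS, beta-cell function, the two myokines, muscle mass and fibre composition are all scheduled for measurement before and after training, so no extra data are needed. The cost is one sentence, best added before the allocation codes are linked to the outcome data.

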**Fig. 3 Fig3:**
[figure not shown]
Conceptual model for the study of the effect of high-intensity/low-volume interval training or continuous exercise training on insulin resistance in patients with metabolic syndrome. The model considers mediator variables such as musclin and apelin, muscle mass and fiber type composition in the thigh; and confounding variables such as age, gender and body mass index

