#### Quantification of serum levels of musclin and apelin

Concentrations of musclin and apelin will be measured in serum using a sandwich-type enzyme linked immunosorbent assay kit (Human Musclin ELISA kit, LifeSpan BioSciences Inc., Catalog number LS-F7799, USA; Human Total Apelin ELISA kit, MyBioSource, Catalog No. MBS-725907, USA). Samples will be taken before and between 44 and 48 h after the last exercise session. Initially, the samples will be stored at − 80 °C, and then for the assay, they will be thawed, and 100 μL will be applied in duplicate to the wells of the ELISA kit. The samples will be incubated at 37 °C; subsequently, the secondary antibody conjugated to biotin will be applied; finally, the samples will be incubated with avidin coupled to an enzyme with peroxidase action. The optical density of each well will be determined in an ELISA reader (Thermo Scientific Varioskan Lux, USA) at 450 nm. The final values will be reported in picograms/milliliter of musclin and apelin.

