Apelin is a myokine involved in the pathophysiology of obesity, IR, diabetes mellitus type 2 and cardiovascular function [52]. Currently, there is controversy about the response of apelin concentrations after exercise interventions [53, 54]. While a study that included patients with diabetes mellitus reported an increase in circulating apelin levels after a CAE program [53], another investigation showed no change after a similar exercise program [54]. In obese men, an HIIT program and a muscle strengthening training program showed an increase in circulating levels of apelin; however, no differences were observed between the two training modalities [27]. We believe that HIIT-low volume may be more effective than CAE in increasing serum concentrations of apelin.

It is recognized that lower thigh muscle mass is associated with metabolic diseases and premature mortality [23, 24] and that the predominance of type II fibers, which is mainly observed in obese people, is related to IR [25]. The findings were inconsistent when body composition and muscle mass were evaluated with DXA before and after a HIIT program [13, 55]. In postmenopausal women, no differences were observed between those assigned to a HIIT program compared to those assigned to a muscle-strengthening program [55]. In men at risk of IR, HIIT, unlike CAE, led to a reduction in body mass, percentage of fat, fat mass and lean mass [13].

The concentration of muscle carnosine is related to the area occupied by type II muscle fibers, the predominant type of fiber in people with metabolic diseases [25]. In turn, the concentration of carnosine in the VLM of the quadriceps is related to IR in sedentary adults [56] and with greater buffer capacity in athletes [57]. It has been reported that muscle carnosine concentrations do not change after HIIT in athletes [58]; however, the adaptive response to exercise is different depending on the level of physical activity and the presence of co-morbidities.

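### For the path model the protocol names only age, gender and BMI as confounders; without baseline HOMA-IR and baseline mediators, the indirect effect can be inflated for any mediator that shifts differently between arms

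*Protocol article*

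**What the plan says.** All references are to the protocol article.

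- **Aim.** The Abstract and Background make mediation the second half of the study aim. Statistical analysis opens the plan for it with "To establish if the musclin, apelin, muscle mass and fiber type composition of the thigh mediate the effect of training on IR".
- **Method.** The same section says: "A model of structural equations will be used with the “path analysis” technique and basic principles proposed in the context of clinical trials". The model is to give total, direct and indirect effects and the percentage explained by the mediator.
- **Mediators and confounders.** The Fig. 3 legend says "The model considers mediator variables such as musclin and apelin, muscle mass and fiber type composition in the thigh", and then "confounding variables such as age, gender and body mass index".
- **Treatment-effect analysis.** "Analysis of covariance (ANCOVA) will be used [45] to estimate the effect of HIIT-low volume compared to CAE on IR, IS" and on the mediators as outcomes. For covariates the section says "The variables used in the minimization procedure (age, gender and BMI) will be included in the analysis".
- **Baseline data.** For the two myokines, "Samples will be taken before and between 44 and 48 h after the last exercise session". HOMA-IR has the same timing (Insulin resistance). Thigh muscle mass and carnosine are measured at the beginning and end of the programme (Measurement of muscle mass; Evaluation of the fiber type composition).

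No section says that baseline HOMA-IR or any baseline mediator enters the path model, or whether final values or changes are modelled there.

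**The concern.** An indirect effect is the product of two paths: arm to mediator, and mediator to IR. Randomisation protects the first. The second compares people who differ on the mediator for any reason, including how they were before training.

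The article itself supplies grounds to expect such pre-training differences. The Discussion relates carnosine in the vastus lateralis to IR in sedentary adults, and the eligibility criteria require a sedentary lifestyle. The Background and Discussion also link type II fibre predominance to IR, and low thigh muscle mass to metabolic disease. If such associations persist to week 12, final mediator and final HOMA-IR are correlated even where training does nothing through that route.

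The three named confounders are the factors used for minimisation. That choice serves the randomised comparison; it was not made for the unprotected path. The strongest candidates for that path are the baseline values of the same variables, and they are not named. At stake is a planned headline result, the percentage of the training effect that each mediator explains.

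**Working it through.** **1. What the plan's own figure implies about baselines.** Sample size gives a difference of 10, SD 15, baseline-final correlation 0.44, 80% power, 5% dropout and 30 per group. With the ANCOVA variance factor and a two-sided 5% level (sidedness is assumed):

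- SD = 15 × √(1 − 0.44²) = 13.47
- n = 2 × (1.96 + 0.84)² × 13.47² / 10², which rounds up to 29 per group
- 29 / 0.95 = 30.5, so 31 per group, close to the stated 30

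A two-sided calculation on final values alone gives 38. (A one-sided calculation on final values gives 30, but ignores the stated correlation.) Baseline adjustment is thus implied for the treatment-effect analysis. Nothing carries it into the path model.

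**2. Size of the bias when there is no true mediation.**

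From the article: 60 patients, 1:1; standardised effect 10/15 = 0.667; baseline-final correlation r = 0.44, given there for insulin sensitivity.

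Assumed, not in the article:

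- correlation ρ between the stable parts of mediator and IR, remaining after age, gender and BMI: 0.3, 0.6 or 0.9;
- r of 0.44 or 0.8, applied to both mediator and IR;
- between-arm shift in the mediator, a: 0 or 0.667 SD;
- total effect on IR of 0.667 SD, in the same direction as the mediator shift.

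Each variable is a stable trait plus independent visit noise, with unit variance and no causal mediator-to-IR path. Within an arm the final values then correlate at ρ × r, so a model on final values without baselines gives

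- false indirect effect = a × ρ × r
- false share of the total effect = a × ρ × r / 0.667, which equals ρ × r when a = 0.667.

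The simulation used one mediator per model and 2,000 trials per cell. Mediation was declared when both paths had |t| > 2. With baselines means the baseline mediator in the mediator equation, and the baseline mediator plus baseline IR in the IR equation. Results for a = 0.667:

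| r | ρ | ρ × r | False share, no baselines | False share, with baselines | False mediation, no baselines | False mediation, with baselines |
|---|---|---|---|---|---|---|
| 0.44 | 0.3 | 0.132 | 0.088/0.667 = 13% | 0.033/0.667 = 5% | 12% | 6% |
| 0.44 | 0.6 | 0.264 | 0.176/0.667 = 26% | 0.075/0.667 = 11% | 38% | 10% |
| 0.44 | 0.9 | 0.396 | 0.265/0.667 = 40% | 0.132/0.667 = 20% | 63% | 25% |
| 0.8 | 0.3 | 0.240 | 0.156/0.667 = 23% | 0.016/0.667 = 2% | 31% | 6% |
| 0.8 | 0.6 | 0.480 | 0.322/0.667 = 48% | 0.045/0.667 = 7% | 70% | 8% |
| 0.8 | 0.9 | 0.720 | 0.477/0.667 = 72% | 0.126/0.667 = 19% | 72% | 32% |

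**3. Boundary cases.**

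- With a = 0, the mean indirect effect is about zero with or without baselines, and false mediation without baselines is at most 5.6%.
- The false share is proportional to a. Half the shift (0.333 SD) halves it, to about 0.5 × 13% = 7% at the low end and 0.5 × 72% = 36% at the high end.
- With change scores, the mean false indirect effect is about zero and false mediation is 3% to 6%. That follows from the additive, constant trait assumed here and need not hold generally.
- Baselines do not remove all the bias, because one baseline measurement is a noisy stand-in for the stable trait.

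**The case against.** A reader might infer that the plan adjusts for these three variables and excludes everything else. The text does not say that. The legend's wording leaves the list formally open, the diagram is not shown, and the model equations may stand in a fuller document. Change scores are not excluded. All of this stands. Against it, the article does not pass over the confounders in silence: it gives a set. The same legend introduces the mediators with the same open wording, and that list is complete at four. The list of confounders most naturally reads as the intended one.

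A reader might also infer that stable correlation between people will itself be reported as mediation, or that it suffices for a mediator to move with training. Neither follows. Both arms train, so a mediator that moves equally in each has no arm-to-mediator effect and gives no mean spurious indirect effect. The Discussion also reports findings that temper the expected shift: no apelin difference between interval and strength training in obese men, and no carnosine change after interval training in athletes. Yet it predicts that HIIT-low volume will beat CAE on musclin, apelin, thigh mass and fibre type, which is the condition under which the bias arises.

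Two further points stand. The correlations that set the size are assumptions; for musclin the article cites only cellular and animal evidence on IR. And inflation presupposes that the confounding acts in the same direction as the hypothesised path; if the signs differ, the bias could mask mediation.

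**Conclusion.** The concern holds in limited form. The plan commits to indirect effects and a percentage explained, names only the minimisation factors as confounders, and does not bring in baseline values that it already collects. If final values are modelled with only those covariates, the result can be inflated for a mediator on which the arms differ.

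The range in the working, 13% to 72% of the total effect falling to 2% to 20%, is conditional on a trait-plus-noise model, the assumed correlations and a mediator shift as large as the effect assumed for insulin sensitivity. It shows that the bias can be material; it does not predict what this trial will find. The documents do not support saying that false mediation will be reported, or that adding baselines restores the nominal error rate: in the cells with a between-arm shift, false mediation was still 6% to 32% after adjustment. The randomised comparison of HIIT-low volume with CAE on IR is not affected.

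**What to change.** State in Statistical analysis and in the Fig. 3 legend that:

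- each mediator equation includes the baseline value of that mediator;
- the IR equation includes baseline HOMA-IR and the baseline values of all four mediators;
- age, gender and BMI stay in every equation;
- or, alternatively, changes from baseline are modelled.

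Keep the planned paths between mediators. The Background hypothesis makes muscle endocrine function depend on muscle mass and fibre type, and models with one mediator at a time could not represent that.

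No new data are needed. The cost is parameters. The IR equation goes from 8 predictors (arm, 4 mediators, 3 covariates) to 13 (plus 5 baselines), with about 60 × 0.95 = 57 patients after dropout, and each mediator equation gains one. Because the bias is reduced and not always removed, the plan should also say that the indirect effects and the percentage explained will be interpreted with residual mediator-to-IR confounding in mind.
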